## Abstract

**Background and Objectives:**

Recombinant human tenecteplase (TNK) tissue-type plasminogen activator (rhTNK-tPA, also named tenecteplase) is non-inferior to alteplase when given up to 4.5 hours after acute ischemic stroke (AIS) within 4.5 hours. Whether intravenous tenecteplase compared with supportive care improves the outcome of patients with AIS due to non-large vessel occlusion (non-LVO) between 4.5-24 hours is uncertain. The Tenecteplase for Acute Non-large vessel occlusion in the Extended Time Window (OPTION) trial aims to test the efficacy and safety of intravenous tenecteplase in patients presenting between 4.5-24 hours after symptom onset who have a non-LVO and evidence of salvageable tissue on perfusion imaging.

**Methods:**

OPTION is a multicenter, prospective, randomized, open-label, blinded endpoint (PROBE) study. Patients with AIS due to non-LVO and evidence of salvageable brain tissue within 4.5-24 hour time window meeting eligibility criteria will be allocated in a 1∶1 ratio to tenecteplase or standard medical treatment. A target mismatch profile is defined as ischemic core volume <50 mL, a mismatch ratio ≥1.2, and a mismatch volume ≥10 mL. A total of 568 patients will provide >80% power to detect a 12% absolute difference in the proportion of patients achieving an excellent functional outcome (modified Rankin scale [mRS] 0-1 at 90 days) at the two-sided 0.05 significance level. The primary efficacy outcome is excellent functional outcome (mRS 0-1) at 90 days. Secondary efficacy outcomes include disability level (ordinal distribution of mRS) at 90 days, functional independence (mRS 0-2) at 90 days, reperfusion at 24 hours, infarct volume at 24 hours, early clinical response at 24 hours, the National Institutes of Health Stroke Scale (NIHSS) change from baseline at 7 days/discharge, health status and quality of life at 90 days. Safety outcomes include symptomatic intracranial hemorrhage within 36 hours, systemic bleeding within 90 days, and mortality within 90 days.

**Discussion:**

The OPTION trial (NCT05752916) will provide evidence regarding the efficacy and safety of tenecteplase 4.5 to 24 hours in patients with AIS due to non-LVO.

## Introduction

Intravenous thrombolysis (IVT) is recommended for acute ischemic stroke (AIS) in eligible patients up to 4.5 h from symptom onset.^[1]^ However, only a small proportion of AIS patients receive IVT, mainly due to the narrow therapeutic time window.^[2]^ An individual patient-level meta-analysis of 8 trials involving IVT without mechanical thrombectomy (MT) for AIS beyond 4.5 h in patients predominantly showing imaging evidence of salvageable tissue demonstrated superior 90-day functional outcomes compared with standard medical care, despite a higher incidence of symptomatic intracranial hemorrhage (sICH).^[3]^ These findings provide evidence-based data to support further randomized controlled trials (RCTs) evaluating IVT in extended time windows for AIS patients with varying vascular occlusion sites.

Five recent RCTs assessed the possibility of extending the IVT time window to 24 h after symptom onset in patients with ischemic stroke.^[4, 5, 6, 7, 8]^ The tenecteplase reperfusion therapy in acute ischemic cerebrovascular events III (TRACE-III) trial demonstrated that in patients with confirmed anterior circulation large vessel occlusion (LVO), extended-window tenecteplase without access to MT achieved superior functional outcomes compared with standard medical care.^[4]^ However, the thrombolysis in imaging-eligible, late window patients to assess the efficacy and safety of tenecteplase (TIMELESS) trial, which also used tenecteplase in the extended time window for patients with anterior circulation LVO, most of whom underwent subsequent MT, did not show improved functional outcomes.^[5]^ Recently, the treatment with intravenous alteplase in ischemic stroke patients with onset time between 4.5 and 24 hours (HOPE) trial evaluated IVT with alteplase in patients with salvageable brain tissue within 4.5 to 24 h, showing functional benefit.^[6]^ The Chinese Acute Tissue-Based Imaging Selection for Lysis in Stroke-Tenecteplase II (CHABLIS-T II) trial revealed that tenecteplase increased reperfusion without symptomatic intracranial hemorrhage in patients selected by imaging in late-time window treatment.^[7]^ The Extending the Time Window for Thrombolysis in Posterior Circulation Stroke without Early computed tomography (CT) Signs (EXPECTS) trial demonstrated that in patients with predominantly mild posterior circulation stroke who did not undergo mechanical thrombectomy (MT), IVT administered 4.5 to 24 h after onset led to superior functional outcomes compared with standard medical care.^[8]^

Despite the progress so far, the efficacy and safety of IVT administered beyond 4.5 h after symptom onset in AIS patients with non-large vessel occlusion (non-LVO) remains inadequately studied. Based on vessel size, large arteries include the internal carotid artery, M1 segment of the middle cerebral artery (MCA), vertebral arteries, and basilar artery.^[9]^ Relative to LVO, AIS presentations related to non-LVO are due to medium vessel occlusion, small vessel (deep and long pial penetrator) occlusion, hemodynamic watershed ischemia, and uncommon or disseminated conditions.^[9, 10, 11]^ The exact prevalence of non-LVOs remains incompletely characterized, as most epidemiological studies lack systematic intracranial vascular imaging protocols. Available data from population-based studies and large clinical registries indicate that approximately 54%-76% of AIS presentations are estimated to be attributable to non-LVO.^[12, 13, 14]^

Advanced imaging may help to select AIS patients who could benefit from IVT in the extended or unknown time window. These advanced imaging techniques include CT or magnetic resonance-based perfusion imaging, as well as magnetic resonance imaging (MRI) with diffusion-weighted imaging-fluid-attenuated inversion recovery (DWI-FLAIR) mismatch.^[15]^ To date, the efficacy and safety of magnetic resonance imaging (MRI)-based thrombolysis in wake-up stroke (WAKE-UP),^[16]^ extending the time for thrombolysis in emergency neurological deficits (EXTEND),^[17]^ TRACE-III,^[4]^ HOPE,^[6]^ and EXPECTS^[8]^ trials have demonstrated the efficacy of IVT beyond the 4.5-hour time window. Four of these trials incorporated advanced imaging selection criteria, while the EXPECTS trial did not mandate advanced imaging-based selection. Notably, 73 (31.2%) were enrolled solely on the basis of clinical presentation and noncontrast CT findings.^[8]^ Based on current evidence, advanced imaging in an extended or unknown time window is still considered as a requirement for providing IVT therapy.^[1,18]^

As the gold-standard thrombolytic agent for AIS since 1995, intravenous alteplase remains a first-line therapy for eligible patients.^[18]^ Recombinant human tenecteplase (TNK) tissue-type plasminogen activator (rhTNK-tPA, also named tenecteplase), a genetically modified variant of alteplase, exhibits higher fibrin specificity and longer half-life, allowing single bolus administration. Recently, at least five phase 3 RCTs demonstrated comparable efficacy and safety profiles of intravenous tenecteplase versus alteplase up to 4.5 h after stroke onset, prompting an update of stroke management guidelines to recommend tenecteplase as one of the preferred thrombolytic agents.^[19, 20, 21, 22, 23]^

We therefore designed the Tenecteplase for Acute Non-large Vessel Occlusion in Extended Time Window (OPTION) trial to investigate the efficacy and safety of intravenous tenecteplase in patients presenting between 4.5-24 h after symptom onset who have a non-LVO and evidence of salvageable tissue on perfusion imaging.

## Materials and methods

### Trial design

OPTION is a phaseⅢ, multicenter, prospective, randomized, open-label, blinded endpoint (PROBE), controlled clinical trial, aiming to investigate the superiority of intravenous tenecteplase, compared with standard medical treatment, to increase 90-day excellent outcome in patients with acute non-LVO stroke and evidence of salvageable brain tissue on baseline computed tomography perfusion (CTP) imaging who are treatable between 4.5-24 h of symptom onset (Figure 1). The OPTION trial is being conducted in compliance with the Declaration of Helsinki principles and is registered at ClinicalTrials. gov (NCT05752916). The protocol has received approval from Institutional Review Boards (IRB) at all participating sites before enrollment (IRB with Xuanwu Hospital, Capital Medical University with number [2022]205). Written informed consent was obtained from all subjects or from their legally authorized representatives before the study. The trial is being performed in approximately 50 centers in China.

**Figure 1 j_jtim-2025-0048_fig_001:**
[figure not shown]
Study Flow Chart. mRS, modified Rankin scale; NIHSS, National Institutes of Health Stroke Scale; CT, computed tomography; CTA, computed tomography angiography; CTP, computed tomography perfusion imaging; rhTNK- tPA, recombinant human tenecteplase tissue-type plasminogen activator; EQ-5D-5L, EuroQoL 5-Dimensions 5-Level questionnaire; BI, Barthel Index.

### Patient population

Patients with AIS due to non-LVO presenting between 4.5-24 h from last-seen-well (including wake-up stroke and unwitnessed stroke), baseline the National Institutes of Health Stroke Scale (NIHSS) from 6 to 25 (or 4 to 5 with disabling deficit) and target mismatch profile on CTP (defined as ischemic core volume <50 mL, a mismatch ratio ≥1.2, and a mismatch volume ≥10 mL) are enrolled into this trial. Based on these imaging criteria, the study population primarily includes patients with acute intracranial non-large vascular occlusions, including the M2 (vertical MCA branches) or more distal segments of MCA, anterior cerebral artery (ACA), posterior cerebral artery (PCA), anterior inferior cerebellar artery (AICA), posterior inferior cerebellar artery (PICA), superior cerebellar artery (SCA), as well as those with large- to medium-vessel stenosis, or a combination of both. The detailed inclusion and exclusion criteria are presented in Table 1.

**Table 1 j_jtim-2025-0048_tab_001:** Inclusion and Exclusion Criteria

Inclusion criteria
Clinical inclusion criteria
□ Clinical diagnosis of acute ischemic stroke
□ Age ≥18 years
□ Pre-stroke mRS score 0-1
□ Disabling stroke, defined as follows:
Baseline NIHSS score 6-25 at the time of randomization, Or NIHSS 4-5 with disabling deficit (*e.g*. hemianopia, aphasia, loss of hand function) as determined by the managing clinician
□ Symptom onset within 4.5-24 h of treatment initiation (onset time refers to “last-seen-well”)
□ Written informed consent from patients or legally responsible representatives
Imaging inclusion criteria
□ Target mismatch profile on CTP defined as an ischemic core volume (using rCBF <30% on CTP) <50 mL, a mismatch ratio (Tmax >6 sec volume to ischemic core ratio) ≥1.2, and a mismatch volume (Tmax >6 sec volume- ischemic core volume) ≥10 mL
Exclusion criteria
Clinical exclusion criteria
□ Treatment with a thrombolytic within the last 72 h or intention to receive IVT
□ Contraindications to thrombolysis
□ Planned or anticipated treatment with EVT
□ Rapidly improving symptoms, particularly if in the judgement of the managing clinician is likely to result in a NIHSS <4 at randomization
□ Pregnancy or lactating; formal testing needed in woman of childbearing potential
□ Cerebral neoplasm (with mass effect)
□ Hereditary or acquired hemorrhagic diathesis, coagulation factor deficiency
□ Impairment in coagulation due to comorbid disease or anticoagulant use. If on warfarin, international normalized ratio (INR) >1.7 or prothrombin time >15 s; if use of any direct oral anticoagulant within the last 48 h; if use of heparin/heparinoid within the last 24 h
□ Use of glycoprotein Ⅱb-Ⅲ a inhibitors within the last 72 h
□ Baseline platelet count <100,000/μL
□ Undergoing hemodialysis or peritoneal dialysis; known severe renal insufficiency with glomerular filtration rate <30 mL/min or serum creatinine >220 mmol/L (2.5 mg/dL)
□ Suspected aortic dissection
□ Major surgery or biopsy within the last 1 month
□ Any active bleeding or recent bleeding within the last 1 month, e.g. gastrointestinal or urinary tract hemorrhage
□ Known severe, life-threatening allergy (more severe than skin rash) to contrast agents
□ Severe, uncontrolled hypertension (systolic blood pressure >185 mmHg or diastolic blood pressure >110 mmHg)
□ Any terminal illness such that the patient would not be expected to survive more than half a year
□ Current participation in any investigational study that may confound outcome assessment of the study
□ Any condition that, in the judgement of the investigator, is inappropriate for participation in the trial or could impose hazards to the patient (*e.g*. inability to understand and/or follow the study procedures and/or follow-up due to mental disorders, cognitive or emotional disorders)
Imaging exclusion criteria
□ Acute intracranial hemorrhage
□ Acute LVO on MR/CT angiography, including ICA, MCA-M1, vertebral artery and basilar artery

CT: computed tomography; CTP: computed tomography perfusion; EVT: endovascular thrombectomy; ICA: internal carotid artery; IVT: intravenous thrombolysis; LVO: large vessel occlusion; MCA: middle cerebral artery; MR: magnetic resonance; mRS: modified Rankin Scale; NIHSS: National Institutes of Health Stroke Scale; rCBF: regional cerebral blood flow; Tmax: time-to-maximum.

### Randomization and blinding

Patients are randomized, in a 1 : 1 ratio, using a minimization process to receive either intravenous tenecteplase or standard medical treatment, stratified by vessel occlusion location (anterior or posterior circulation), age (<65 or ≥65 years), baseline NIHSS (<16 or ≥16) and center. The randomization will be done by a computerized central interactive web response system. All endpoints will be evaluated by an independent investigator who is unaware of the treatment group.

### Intervention

Patients allocated in the interventional arm will receive intravenous tenecteplase at 0.25 mg/kg, not exceeding a maximum dose of 25 mg. Each vial of tenecteplase is reconstituted with 3 mL of sterile water for injection and injected based on body weight in a single bolus over 5-10 seconds.

Patients allocated in the control arm will receive antiplatelet therapy (aspirin or clopidogrel alone) at the discretion of local investigators.

All enrolled patients are treated according to the *2023 Chinese Guidelines for Diagnosis and Treatment of Acute Ischemic Stroke* and *2022 Chinese Guideline for the Secondary Prevention of Ischemic Stroke and Transient Ischemic Attack*.^[24,25]^ Patients who are planned or anticipated to be treated with endovascular thrombectomy (EVT) are excluded from the trial. No antiplatelet therapy (*e.g*. aspirin, clopidogrel, ticagrelor, or glycoprotein IIb/IIIa inhibitors) should be administered within 24 h after tenecteplase. Oral or parenteral anticoagulants (*e.g*. warfarin, dabigatran, heparin, low molecular weight heparin, argatroban) are prohibited for the first 24 h in both arms. Close attention should be paid to patient’s changes of symptoms and signs in order to detect bleeding events in time. The management of bleeding events should follow the clinical routine and be taken immediately.

### Clinical and imaging evaluation

Study visits are performed at the screening period, 0 h, 24 (-2/+12) hours, 48 (±6) hours, 7 (±2) days/discharge (whichever is earlier), and 90 (±7) days. During the screening period, all participants undergo CT, computed tomography angiography (CTA), and CTP after clinical evaluation. Clinical examination and radiological follow-up with CT, CTA, and CTP are performed at 24 (-2/+12) hours. If symptom deterioration with suspected intracranial hemorrhage occurs during hospitalization, an immediate CT scan should be performed. A non-contrast CT is recommended to be done, if possible, at 7 (±2) days or at discharge. At baseline and follow-up visits, clinical evaluation includes vital signs, concomitant medications, NIHSS and modified Rankin Scale (mRS) score. At 90 (±7) days, mRS, EuroQoL 5-Dimensions 5-Level questionnaire (EQ-5D-5L) and Barthel Index (BI) are assessed *via* a standardized telephone interview. All trial procedures are summarized in Table 2.

**Table 2 j_jtim-2025-0048_tab_002:** Trial Schedule

Procedure/Investigation	Screening	Treatment	Follow-up			
	V0	V1	V2	V3	V4	V5
Time	Baseline	0 h	24 (-2/+12) h	48 (±6) h	7 (±2) days/discharge^g^	90 (±7) days
Informed consent	X					
Inclusion/exclusion criteria	X					
Demographic data^a^	X					
Medical history^b^	X					
Concomitant medication	X		X	X	X	X
Vital signs^c^	X		X	X	X	
ECG	X					
Laboratory tests^d^	X		X			
Imaging^e^	X		X		X^*^	
mRS^f^	X				X	X
NIHSS	X		X	X	X	
GCS	X		X	X	X	
EQ-5D-5L						X
BI						X
Randomization	X					
Study medication administration		X				
AEs/SAEs		X	X	X	X	X
Study completion						X

AEs: Adverse Events; BI: Barthel index; ECG: electrocardiography; EQ-5D-5L: EuroQoL 5-Dimensions 5-Level questionnaire; GCS: Glasgow Coma Scale; mRS: Modified Rankin Scale; NIHSS: National Institutes of Health Stroke Scale; SAEs: Serious Adverse Events. ^a^: Demographic data include date of birth, sex, ethnic group, body height, body weight. ^b^: Medical history includes history of present illness, past medical history, family history, drug allergies, smoking and alcohol use. ^c^: Vital signs include temperature, blood pressure and heart rate. ^d^: Laboratory tests include hematology, liver and renal function, coagulation profile and glucose; pregnancy test is limited to women of child bearing potential. ^e^: Brain CT+CTA+CTP. ^f^: Baseline mRS is defined as a pre-stroke score. ^g^: Whichever is earlier. *: Repeat CT is recommended, if possible; if symptom deterioration with suspected intracranial hemorrhage occurs during hospitalization, an immediate CT scan should be performed; X: The assessment required at each time point.

If a suspected or confirmed serious adverse event (SAE) occurs, necessary assessments should be performed according to the protocol. The SAEs will be reviewed by the Clinical Events Committee (CEC).

### Primary outcome

The primary outcome is the proportion of excellent functional outcome defined as an mRS of 0-1 at 90 (±7) days.

### Secondary outcomes

There are seven secondary outcomes, (1): Disability level (ordinal mRS score) at 90 (±7) days; (2): Proportion of functional independence (mRS of 0-2) at 90 (±7) days; (3): Proportion of reperfusion at 24 (-2/+12) h, defined as >90% reduction in Tmax >6 s lesion volume by CTP; (4): Infarct volume at 24 (-2/+12) h, measured by CT scan at 24 (-2/+12) h; (5): Proportion of early clinical response at 24 (-2/+12) h, defined as a NIHSS score of 0 or 1 or NIHSS drop of ≥8 from baseline; (6): NIHSS change from baseline at 7 (±2) days/discharge (whichever is earlier); (7): Health status and quality of life (EQ-5D-5L) at 90 (±7) days.

### Safety outcomes

The safety outcomes are (1): Proportion of patients with sICH within 36 h, as defined by Heidelberg bleeding classification;^[26]^ (2): Proportion of systemic bleeding within 90 (±7) days, as defined by The Global Utilization of Streptokinase and Tissue Plasminogen Activator for Occluded Coronary Arteries (GUSTO): moderate and severe bleeding; (3): Mortality within 90 (±7) days.

### Sample size estimation

The sample size is based on the primary outcome. Based on the reported pooled data of the stroke thrombolysis trials in the extended time window,^[27]^ we expect a 12% absolute difference in the proportion of patients reaching the primary outcome between patients treated with tenecteplase and standard medical treatment (expected rate of excellent functional outcome 50% in patients treated with tenecteplase and 38% in patients treated with standard medical treatment). Considering the potential impact of one interim efficacy analysis on the probability of type I error, we adjusted the alpha error to a two-sided alpha of 0.049. The total sample size of 568 (*n* = 284 per treatment group) will have 80% power to detect the specified difference at the two-sided 0.049 significance level, with a 5% dropout rate.

One efficacy interim analysis is planned when 50% of the target sample size has completed 90-day follow-up. A Lan-DeMets alpha spending function will be used to control the overall alpha level, using O’Brien and Fleming boundaries (corresponding to an alpha level of 0.003 and 0.049 at the interim and final analysis, respectively).

### Statistical analysis

The analysis population for the efficacy analyses will be performed on the intention-to-treat (ITT) population. For the primary outcome, the proportions of mRS 0-1 at 90 (±7) days will be compared between two treatment groups using a modified Poisson regression. The risk ratio (RR) and its 95% confidence interval (CI) will be reported. We will also perform adjusted analysis of the primary outcome with adjustment for pre-specified covariates.

The distribution of mRS score at 90 (±7) days will be analyzed using ordinal logistic regression, with treatment effect reported as a common odds ratio and its corresponding 95% CI. If the proportional odds hypothesis is rejected, the generalized odds ratio (GenOR) with 95% CI will be calculated. For binary secondary efficacy endpoints, modified Poisson regression model will be employed to determine RR and its 95% CI. For continuous secondary efficacy endpoints, linear regression models will be employed to estimate mean difference as a measurement of treatment effect. In case the normality assumption for the residuals is violated, win ratio will be calculated. Safety analyses will be performed on the safety population who received one of the study interventions according to the treatment they actually received. Safety endpoints will be compared using the modified Poisson regression. Subgroup analyses include age (<65 years and ≥ 65 years), time from symptom onset (last-seen-well) to randomization (>4.5-9 h and >9-24 h and stroke on awakening), baseline NIHSS score (<10 and ≥10), vessel occlusion location (anterior circulation and posterior circulation), occlusion site (M2 segment of MCA, M3-M4 segment of MCA, ACA, PCA and stenosis), baseline serum glucose (<100 mg/dL and ≥100 mg/dL) and baseline systolic blood pressure (≤140 mmHg and >140 mmHg).

Three safety interim analyses were planned when the first 100, 200, 300 patients have completed the 90-day follow-up. One efficacy interim analysis was planned to be conducted when 50% of the total patients have completed the 90-day follow-up. All statistical analyses will be performed following a statistical analysis plan (SAP) which will be finalised before the database lock and unblinding of the trial. SAS software version 9.4 (SAS Institute) and R version 4.4.1 will be used for the statistical analyses.

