### Data safety and monitoring board

An independent data safety and monitoring board (DSMB) will regularly monitor the safety of the trial and guarantee the safety of all patients. The DSMB will perform safety reviews when the first 100, 200 and 300 patients are enrolled and complete 90-day follow-up. If there are concerns about safety, the DSMB will make a recommendation to the trial steering committee about continuing, stopping or modifying the trial. One prespecified efficacy interim analysis will be performed when 284 patients have completed 90-day follow-up. Results of the interim analysis will only be presented to the DSMB.

Due to the fast speed of enrollment, after review with the DSMB in June 2025, the original interim analysis plan was considered no longer to serve its purpose. On the recommendation of the DSMB, the steering committee rescinded the planned efficacy interim analysis and the third safety analysis. Since no formal assessment of efficacy is done and no alpha is spent, we will not adjust the alpha level or p values for the final analysis.

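### The primary test leaves out the prognostic factors used in the minimisation; adjusting for age, NIHSS and circulation would gain about 0 to 6 points of power at no cost in patients

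*Protocol article*

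**What the plan says.** Under Randomization and blinding, patients are allocated 1:1 "using a minimization process to receive either intravenous tenecteplase or standard medical treatment", and the process is "stratified by vessel occlusion location (anterior or posterior circulation), age (<65 or ≥65 years), baseline NIHSS (<16 or ≥16) and center".

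Under Statistical analysis, the proportions with mRS 0-1 at 90 days "will be compared between two treatment groups using a modified Poisson regression", reported as a risk ratio with a 95% CI. No covariate is named for this comparison. The article then adds: "We will also perform adjusted analysis of the primary outcome with adjustment for pre-specified covariates". The word unadjusted does not appear, but an adjusted analysis that is performed as well implies that the main one is not adjusted.

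The sizing under Sample size estimation fits that reading. It is a plain two-proportion calculation that takes no credit for covariates.

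**The concern.** A factor is normally chosen for minimisation because it is expected to predict outcome. If it does, leaving it out of the primary model has two separate consequences.

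- **Balanced part.** Minimisation removes the between-arm variation due to the categories it balances. The unadjusted robust standard error does not know this, so it is somewhat larger than the true sampling SD. The test then runs a little below its nominal level.
- **Unbalanced part.** Age is balanced only at 65 and NIHSS only at 16, while eligibility runs from NIHSS 4 to 25. Variation within those categories is left to chance. The unadjusted standard error counts it correctly, so nothing is misstated, but precision that adjustment would recover is lost.

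The trial is sized at 80% power with no visible reserve, so free precision is worth having. Chance imbalance in NIHSS below 16 also feeds into the headline risk ratio, and the article's own subgroup cut for NIHSS is 10.

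**Working it through.** **Inputs from the article.** The rates are "expected rate of excellent functional outcome 50% in patients treated with tenecteplase and 38% in patients treated with standard medical treatment". For alpha, "we adjusted the alpha error to a two-sided alpha of 0.049". There are 284 patients per arm, 5% dropout and about 50 centres. The efficacy interim was later rescinded and "we will not adjust the alpha level or p values for the final analysis", which I read as a final two-sided 0.05.

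**Inputs assumed.** The article gives no prognostic strength and no distribution of age or NIHSS. R² below is the assumed share of outcome variance explained.

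**1. Reproduce the planned size.** n per arm = [z(α/2)·√(2·0.44·0.56) + z(0.80)·√(0.50·0.50 + 0.38·0.62)]² / 0.12², with α = 0.049. This gives 270 per arm, or 540 evaluable. Then 270 × 1.05 = 283.5, rounded up to 284 (568 in total), while 270/0.95 gives 285 (570). The stated 568 reproduces. Power with 270 per arm is 80.1% at 0.049 and 80.4% at 0.05.

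**2. Normal approximation when the balanced categories carry all of R².** Let k = √(1−R²), s₀ = √(2·0.44·0.56/270) = 0.0427 and s₁ = √(0.4856/270) = 0.0424.
- True level, unadjusted: 2·[1 − Φ(1.96/k)]
- Power, unadjusted: Φ[(0.12 − 1.96·s₀)/(k·s₁)]
- Power, adjusted: Φ[(0.12 − 1.96·k·s₀)/(k·s₁)]

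| R² | True level, unadjusted | Power, unadjusted | Power, adjusted |
|---|---|---|---|
| 0 | 0.050 | 80.4% | 80.4% |
| 0.05 | 0.044 | 81.0% | 82.3% |
| 0.10 | 0.039 | 81.6% | 84.3% |
| 0.20 | 0.028 | 83.0% | 88.3% |

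The level column is an extreme, because two-level factors do not carry all the information in age and NIHSS.

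**3. Separate the two parts.** Let R²b be the share carried by the balanced categories and R² the share carried by the continuous covariates. The unadjusted standard error is too wide only by 1/√(1−R²b). As an illustration, assume R²b = 0.03 and R² = 0.10.
- The standard error is too wide by 1/√0.97 = 1.015, and the true level is 2·[1 − Φ(1.990)] = 0.047.
- Unadjusted power is Φ(0.868) = 80.7%.
- Adjusting for the categories alone gives Φ(0.899) = 81.6%.
- Adjusting for the continuous covariates gives 84.3%.

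In this example most of the gain comes from the continuous terms.

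**4. Simulation of minimisation with two-level factors.** 540 patients, 50 centres, an assumed 0.85 biased coin, 4,000 trials per cell, robust-variance Poisson, two-sided 0.05. The assumed share with NIHSS ≥16 is 12%, but 25% in the last row.

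| R² | Type I error, unadjusted / adjusted | Power, unadjusted / adjusted | Unadjusted SE ÷ true SD (at 50% vs 38%) |
|---|---|---|---|
| 0 | 0.050 / 0.051 | 80.4% / 80.3% | 1.00 |
| 0.03 | 0.048 / 0.052 | 81.5% / 81.6% | 1.00 |
| 0.08 | 0.047 / 0.053 | 81.4% / 82.9% | 1.04 |
| 0.18 | 0.033 / 0.052 | 83.4% / 87.8% | 1.12 |

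Simulation error is about √(0.05·0.95/4000) = 0.003 on the level and √(0.8·0.2/4000) = 0.6 points on power, so the adjusted levels are compatible with 0.05.

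**5. Simulation with continuous age and NIHSS, minimised at the trial's cut-points.** Covariate distributions are assumed.
- With 4 to 8% of patients at NIHSS ≥16 and AUC 0.68 to 0.76, the unadjusted type I error was 4.1 to 4.9%.
- With about 14% at NIHSS ≥16 and AUC 0.73 to 0.79, it was 3.8 to 4.0%.
- Continuous adjustment gained about 1.4 to 2.2 points of power at AUC 0.63 to 0.66 and 3 to 6 points at AUC 0.68 to 0.79.
- A separate run with about 8% at NIHSS ≥16 gave an unadjusted standard error about 0 to 4% too wide, type I error near 4.2 to 4.3%, a power gain of about 0 to 6 points, and an unchanged average risk ratio.

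**The case against.** The best defence is that the article makes a choice and commits no error. An unadjusted primary comparison with a pre-specified adjusted analysis beside it is common and valid. The error is in the safe direction, and the simulated unadjusted power stays at or slightly above 80%. The covariate list belongs in the SAP, which is not shown, and its absence here is no finding. The word unadjusted is itself an inference from a condensed text.

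Most of this stands and sets the weight of the point. It does not remove it, because the article does fix which model is primary, and the point concerns that choice.

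Three stronger readings are tempting but are not supported:

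- **That the confidence interval is too wide as a matter of fact, with type I error around 3.2 to 3.9%.** Rates that low arise when allocation is balanced on a single cut of the whole prognostic score, or when the balanced categories are very strong (the last row of step 4). The trial minimises on separate two-level factors and centre. The excess depends on how many patients score 16 or more, which the article does not give.
- **That NIHSS variation below 16 makes the standard error too wide.** It does not. That variation is correctly included and costs precision only.
- **That the trial is underpowered through this choice.** Under its own assumptions it is not. What is forgone is power above the target.

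Nor does changing the order of the two analyses prevent them from disagreeing. It only settles which one governs.

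**Conclusion.** The point holds as a matter of efficiency. If the minimisation factors predict mRS 0-1, the unadjusted primary test is mildly conservative and less precise than it could be, mainly because it ignores continuous age and NIHSS. The gain from adjustment is about 0 to 6 points of power. It is close to zero if the factors are weak and several points only if they are moderate to strong. The range rests on assumed prognostic strength and covariate distributions and on 540 evaluable patients at 38% versus 50%. Validity is not in question: the average risk ratio is unchanged, type I error is not inflated, and the planned 80% power is about met. The change is worth making because it is almost free.

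**What to change.** In the SAP, before database lock and unblinding, name as primary the modified Poisson model with treatment, continuous age, continuous baseline NIHSS and anterior/posterior circulation. Handle centre by a random effect, by clustering or by pooling small centres. With about 50 centres there are roughly 568/50 ≈ 11 patients each, too few for a fixed effect per centre. Report the unadjusted risk ratio with its 95% CI as supportive, and state that the adjusted result governs if the two differ.

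The cost is about one sentence in the SAP and a matching note wherever the primary analysis is described. No further patients or data are needed, because age, NIHSS and circulation must already be known to run the minimisation. The sample size need not change.
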